#### Study procedures

2.4.8

The intervention will be implemented through a structured approach involving community engagement, capacity building of frontline workers, and systematic delivery of intervention components, supported by robust monitoring mechanisms.

##### Community sensitization

2.4.8.1

Prior to commencement, orientation meetings will be held at each study site/cluster to orient key stakeholders, including panchayat members, Poshan Panchayat representatives, mothers’ groups, and the village health, sanitation and nutrition committee on study objectives, intervention package, activities, and the limited area approach, to secure community support and engagement.

##### Training of anganwadi workers and helpers

2.4.8.2

In intervention clusters, AWWs and AWHs will undergo comprehensive training on the improved THR and delivery of the SBCC package. Training will include classroom sessions, on-field demonstrations, and on-the-job support using local language materials, case studies, group exercises, and videos. Supportive supervision from the study team will reinforce skills. Health functionaries in intervention clusters, including ASHAs and ANMs, will be oriented on improved THR and trained on SBCC strategies to complement ICDS activities. Joint sessions for ICDS and health staff may be organized as needed. Training will occur before intervention rollout, with planned refresher sessions at 3–4 and 6–8 months of initiation of the intervention, and additional sessions as needed to appropriately cater to the age-based changes in the dietary and behavioural practices.

AWWs and AWHs in the comparison clusters will not be given any additional training other than orientation about the study activities.

##### Delivery of intervention package

2.4.8.3

The intervention package will be delivered through the existing ICDS platform. The home visit sessions of AWW will be utilized to deliver the integrated intervention package. AWWs in intervention clusters will distribute prescribed quantities of the improved THR fortnightly to eligible households (aligned with the existing THR supply guidelines for amount and frequency) and counsel caregivers and family members on its role in child growth. Improved THR packets will be supplied monthly to AWCs based on beneficiary numbers. Improved SBCC will have special emphasis during the home visits in addition to the improved THR distribution. The AWWs will be trained to be active listeners, more reflective and adaptive to the household needs, rather than just being directive and information sharing. AWWs will distribute Information, Education, and Communication (IEC) materials, including locally appropriate cookbooks in the local language, to help caregivers add variety to their preparations (taste/palatability), as well as promote IYCF and WASH practices. If any illness or sickness is identified during the child’s participation in the trial, the study team will ensure that the child is promptly referred to the nearest government healthcare facility for appropriate care.

##### Health, early child development, and related activities

2.4.8.4

AWWs, ANMs, and ASHAs will continue routine health and early child development services in all clusters. In intervention clusters, caregivers will be counselled on immunization, WASH, care during childhood illnesses, and participation in Village Health and Nutrition Days (VHNDs), with iron and folic acid supplementation and deworming as per guidelines. In comparison clusters, the WCD and health functionaries will continue to provide the services as usual.

#### Data collection

2.4.9

Data will be collected using appropriate tools to assess primary and secondary outcomes.

##### Anthropometric assessment

2.4.9.1

Standard guidelines proposed by the WHO will be followed to assess anthropometric indicators (47). Weight will be measured using calibrated electronic weighing scales (seca 354) with a precision of 10gm. The length/height will be measured using a standardized measurement board/infantometer (seca 417)/stadiometer (seca 213) with a precision of 1 mm. The child’s MUAC will be measured using a non-stretchable tape (seca 201) with a precision of 1 mm. At one of the study sites, Hoshangabad, MUAC will be measured using standard colour-coded tapes supplied by UNICEF (48).

##### Infant and young child feeding practices

2.4.9.2

Data on IYCF practices, including breastfeeding and complementary feeding, will be collected using a structured IYCF questionnaire, along with a 24-h dietary recall survey. WHO recommended core indicators of optimal breastfeeding, including exclusive breastfeeding till 6 months, continued breastfeeding for at least two years post-birth, along with complementary feeding practices, such as introduction of solid, semi-solid, or soft foods, minimum dietary diversity, minimum meal frequency, minimum acceptable diet, consumption of iron-rich or iron-fortified foods from postnatal 6 completed months and nutrient intake will be captured (49). Apart from a pre-tested questionnaire on IYCF practices, a two non-consecutive 24-h dietary recall survey will be administered on the mother/primary caregiver for assessing the dietary and nutrient intake of children enrolled for the longitudinal study. Respondents will include mothers and/or primary caregivers within the household. During this dietary survey, respondents will be asked to recall a detailed food intake of the child during the past 24 h. A standard food recall kit (measuring cups, spoons and food picture flip book) will be used by the interviewer for portion size estimation.

Household food security information will be collected using a questionnaire adapted from the food security and nutrition surveillance tool (50, 51).

##### WASH-related knowledge, attitude, and practices (KAP)

2.4.9.3

Data on WASH will be collected using a KAP questionnaire developed based on a standard manual for WASH (3).

##### Health status

2.4.9.4

The children’s morbidity data (e.g., diarrhoea and acute illnesses) will be collected using a 2-week recall questionnaire along with any hospitalization history. The vaccination data would be recorded based on the Essential Program on Immunization (EPI) schedule, verified from the immunization card or register with AWC/ASHA/ANM (52).

##### Economic evaluation

2.4.9.5

The cost-effectiveness of the intervention will be conducted from a government provider perspective. The incremental economic cost of the intervention will be calculated using an ingredients approach, where each activity related to the intervention will be identified and costed. For example, for community engagement, there will be several stakeholder engagement meetings with panchayats members, community members, and mothers’ groups. Further, ANMs, ASHAs, AWWs and AWHs will be trained as part of the intervention. These activities from each study site will be documented in detail for cost analysis. Financial costs under each study activity will include actual expenses related to the intervention (e.g., expenses for staff training, SBCC materials, prescribed quantities of improved THR, etc.). Economic costs include financial costs and time costs related to various intervention activities. For example, hours spent by AWWs, AWHs during training, hours spent by AWWs during improved THR distribution and SBCC will be multiplied by the hourly wages of AWWs and AWHs to estimate the time costs of the activities. While actual expenses related to the intervention will be collected from financial records of each site, time spent data will be collected through interviews with key stakeholders such as AWWs and AWHs. Data will be collected alongside intervention development and roll-out using structured questionnaires. The total cost of the intervention site will be the sum of the financial and time cost of all activities related to intervention development and implementation. As the intervention will be compared with the existing THR and SBCC, the costs incurred for the intervention will be the incremental cost. Incremental effectiveness will be measured by examining the changes in weight-for-age z-score for children in the intervention and control arms. The cost-effectiveness ratio will be the incremental cost of the intervention/additional number of children with a mean difference of 0.3 in mean WAZ scores in the intervention arm as compared to the control arm.

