### Phase I: formative research

2.2

Exploratory research will be undertaken over a period of six to seven months to assess the current status of complementary feeding practices and THR implementation and uptake, and to generate context-specific, evidence-based insights. The research will be driven by four key objectives:(1) to assess the current provisions, quality, implementation, and uptake of THR under ICDS program in selected states; (2) to explore the perceptions of key stakeholder including policymakers, program implementers, frontline workers, vendors, and civil society members regarding the challenges and gaps in the THR products and program implementation; (3) to assess IYCF feeding and dietary practices, including locally prevalent, traditional, and culturally embedded complementary feeding practices, and positive feeding behaviours among children aged 6 to 36 months, and to document perspectives of caregivers and key community stakeholders; and (4) to evaluate the nutritional and chemical profile of the existing THR products. These objectives will be achieved through various activities outlined in Table 2.

**Table 2 tab2:** Components of formative research.

Activity	Tools/methods	Key outputs
Review of existing literature	Desk review	THR policies, guidelines, composition, supply chain, SBCC strategies, best global practices, and relevant SBCC theories/models
Mapping of the THR supply chain and key stakeholders engaged in the selected district	Net mapping tool (32); Key informant interviews (KIIs) with the stakeholders identified through stakeholder mapping and snowball sampling.	Current THR provision (ingredients, nutrition profile), end-to-end supply chain from procurement to distribution, logistics and costs, etc.
Observations related to program implementation	Observation checklists; In-depth interviews (IDIs) and KIIs.	Existing training standards, adequacy of personnel, infrastructure, and SBCC strategies.
Qualitative inquiries with supply-side stakeholders	IDIs, focused group discussion (FGDs) (until data saturation).	Perceptions of supply-side actors (program implementers, frontline workers like anganwadi workers (AWWs), anganwadi helpers (AWHs), vendors, civil society members, SHG, etc.) on challenges and gaps in current THR composition and SBCC delivery.

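### The cost-effectiveness numerator is the whole cost of the intervention; nothing is subtracted for the existing THR and SBCC, so the ratio is not incremental

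*Protocol article*

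**What the plan says.** Objective 3, at the end of the Background, is incremental: the package is to be judged on cost-effectiveness against the existing take-home ration (THR) and the existing social and behaviour change communication (SBCC).

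The method is in section 2.4.9.5, Economic evaluation. The analysis "will be conducted from a government provider perspective". Financial costs are exemplified by "expenses for staff training, SBCC materials, prescribed quantities of improved THR, etc". For time costs, "hours spent by AWWs during improved THR distribution and SBCC will be multiplied by the hourly wages of AWWs and AWHs". The total is the financial plus time cost of "all activities related to intervention development and implementation". The section then states: "As the intervention will be compared with the existing THR and SBCC, the costs incurred for the intervention will be the incremental cost".

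Three other places bear on this:

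- Section 2.4.4, Intervention: comparison clusters stay on the current ration and counselling under ICDS, unchanged.
- Section 2.4.8.3, Delivery of intervention package: the improved ration goes out through the existing ICDS platform, "aligned with the existing THR supply guidelines for amount and frequency".
- Section 2.2, Table 2: the formative phase is to describe the current ration's "end-to-end supply chain from procurement to distribution, logistics and costs".

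**The concern.** An incremental cost is the difference in cost between two alternatives. The full cost of one alternative equals that difference only if the other costs nothing, or if the new package is added on top of the old one with nothing displaced. The protocol points away from both. The comparator is an active ration and counselling programme run by the provider whose perspective is taken, and the improved ration is governed by the same supply guidelines as the existing one.

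The two halves of the ratio are also built differently. The effect is measured from both arms; the cost comes from the intervention arm alone.

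At stake is the headline figure for objective 3. The trial is meant to inform ration reform, and a ratio that charges the new package for food and worker time the government already buys makes it look less economic than it is. The error always runs in that direction.

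**Working it through.** The protocol gives no unit cost and no expected ratio, so there is no figure to reproduce. The check is algebraic, followed by an illustration on assumed costs.

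**Inputs by source**

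- T: improved ration plus worker time on its delivery (2.4.9.5, listed gross).
- A: activities that are truly added, such as extra training, new materials and community meetings (2.4.9.5, 2.4.8.1, 2.4.8.2).
- D: development cost (2.4.9.5, included in the total).
- E: cost of the existing THR and SBCC displaced in intervention clusters (existence implied by 2.4.4 and 2.4.8.3; no step in 2.4.9.5 measures or subtracts it).

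**Formulas**

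- Numerator as planned: T + A + D.
- Incremental numerator: T + A + D − E.
- Excess: (T + A + D) − (T + A + D − E) = E.
- Overstatement of the ratio, with the denominator unchanged: (T + A + D) / (T + A + D − E).

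The factor exceeds 1 for any E above zero while the total exceeds E. It equals 1 only if E = 0.

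**Illustration (all values assumed)**

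Set T = 100, A = 10 or 50, D = 0 or 20, and E = r × 100, where r is the displaced cost as a share of T. Development stays in both numerators. The low end uses A = 50, D = 20; the high end uses A = 10, D = 0.

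| r | Low end | High end |
|---|---|---|
| 0 | 170/170 = 1.0 | 110/110 = 1.0 |
| 0.25 | 170/145 = 1.2 | 110/85 = 1.3 |
| 0.5 | 170/120 = 1.4 | 110/60 = 1.8 |
| 0.75 | 170/95 = 1.8 | 110/35 = 3.1 |
| 0.9 | 170/80 = 2.1 | 110/20 = 5.5 |

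**Role of development cost**

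Take r = 0.5 and A = 10. Without development the factor is 110/60 = 1.8. With D = 20 kept in both numerators it falls to 130/80 = 1.6. With D = 20 removed from the corrected numerator only, it rises to 130/60 = 2.2. Development therefore enlarges the discrepancy only if one has already decided that it does not belong in the ratio.

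**The case against.** **The sentence may mean added costs only.** On that reading the opening clause of the rule signals that only extra costs count. The listed ingredients do not fit: the whole quantity of improved ration and the hours spent distributing it have direct counterparts in the comparison arm. No netting step is described. This is also not a detail lost in condensing a longer protocol, because the article states a definition and the definition is wrong.

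**Replacement is inferred.** This stands in part. Supplementary Table 2 is not shown. Shared amount and frequency guidelines make replacement of the ration likely, but how much counselling and worker time is replaced, and how much is added, is unknown. Training, materials and meetings are real increments with nothing to offset them. Full replacement should not be asserted as fact.

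**Development cost.** A reader might infer that including it is a second error, because a government adopting the finished package would not pay it again. The document does not support that. The package is deliberately specific to state and district, so extension elsewhere could require some of this work again. Including it is a defensible choice, and the section does not say that the formative research is costed.

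**Size.** A reader might attach a large multiple to the bias, even tenfold. That needs existing services to cost 90% of the improved package's entire running cost, since 1/(1 − 0.9) = 10. Nothing in the document supports such a share, or any other.

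**Usefulness.** It would also go too far to say that the evaluation could not inform reform. Costs are documented by activity at each site and Phase I records current supply-chain costs, so the ration part could be netted at analysis. The bias cannot make a poor package look cost-effective.

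**Conclusion.** The concern holds for the missing subtraction. Section 2.4.9.5 equates intervention cost with incremental cost, which conflicts with objective 3 and inflates the numerator by the existing cost displaced. The direction is certain if any existing cost is displaced, which sections 2.4.4 and 2.4.8.3 make likely. The size cannot be computed from the document; the factors above rest wholly on assumed costs and show only that the effect could be small or several-fold.

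This should be fixed but is not critical. Cost-effectiveness is a secondary objective, and the primary weight-for-age comparison, the randomisation and the sample size are untouched.

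**What to change.** Replace the rule in section 2.4.9.5 with a definition along these lines: incremental cost is the cost of improved THR and SBCC minus the cost of existing THR and SBCC, over the same period and per comparable child. State that activities with no counterpart in the comparison arm (extra training, new materials, additional meetings) count in full.

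Collect existing ration cost, existing SBCC cost and the time of anganwadi workers and helpers in comparison clusters, with the same questionnaires and interviews, at the economic data points that Table 3 already schedules from baseline to month 24. This should be prospective, because worker time comes from interviews and is hard to recover later.

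Use the Phase I supply-chain costs only as support. They precede the trial, they come from areas that section 2.4.1 excludes from it, and Table 2 does not list worker time or the cost of existing SBCC.

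Optionally, show development cost on its own line and report the ratio with and without it.

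The price is a reworded definition and a modest amount of extra costing work in comparison clusters.

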2. To evaluate the effect of the intervention package targeted at children aged 6–36 months (and their caretakers/households) compared to the existing THR and SBCC strategy after 18 months of implementation on length/height-for-age z score (LAZ/HAZ), weight-for-height/length z score (WHZ/WLZ), the prevalence of underweight (WAZ < -2SD), wasting (WHZ/WLZ < -2 SD), stunting (LAZ/HAZ < -2 SD), infant and young child feeding practices (IYCF) (such as minimum meal frequency, minimum dietary diversity, and minimum acceptable diet), child morbidity indicators, and caregiver knowledge, skills, practices, and behaviour towards infant and young child feeding practices.3. To document the incremental cost-effectiveness of the integrated intervention package compared to the existing THR and SBCC strategy in the study districts.

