#### Study participants

2.4.3

All the children aged 6–36 months who live in the selected AWC area, registered with the AWC and regardless of their socioeconomic status, will be eligible to receive the THR and SBCC, according to the allocation arms. The quantity of THR that they will receive will be based on ICDS guidelines, considering both their age and nutritional status (normal, MAM, or SAM). There are no exclusion criteria. For the children not registered in the AWCs, the caregivers and household head will be counselled for registration in the AWC.

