#### Sample size

2.4.6

The sample size is calculated to detect a minimum mean difference of 0.3 in mean WAZ score between intervention and comparator arms, assuming a mean WAZ of −1.8 in the comparator group and a standard deviation of 1.0 in both groups (45, 46). With 80% power, 5% significance level, an intra-cluster correlation coefficient of 0.05, and an expected attrition rate of 20%, the estimated sample size is 300 per arm per site. This will be achieved through 30 clusters per arm, with an average of 10 children per cluster.

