#### Randomization and blinding

2.4.7

The unit of randomization will be HSC, as a proxy for the AWC. Sixty HSCs/HWCs from different blocks in the district will be identified using simple random sampling. Under each selected HSC, the eligible AWC, as per the eligibility criteria described in the earlier section, will be selected using simple random sampling for the implementation of study activities. To meet the required number of children in the eligible age groups in areas such as hilly/tribal/sparse habitation, more than one AWC (contiguous AWCs covering about 1,000–1,200 population) may be included, which will be considered as one cluster. For the larger villages/urban areas with more than one AWC, only one AWC (with a population of about 1,000–1,200) will be selected for inclusion in the study. While selecting the AWCs from the HSCs, it will be ensured that the AWCs selected from different HSCs are drawn from areas not involved in pilot studies, non-contiguous, and are located at a reasonable distance to minimize contamination.

Selected HSCs and 60 AWC units (clusters) will be randomized into the two arms by an independent statistician; 30 into the intervention arm and 30 into the comparison arm. Randomization will be stratified by the blocks included, such that every HSC/AWC randomized to the intervention arm will have an HSC/AWC randomized to the control arm from the same block. For randomization, pair matching of clusters will be done considering key parameters such as location stratum (urban–rural) and population size. Within each matched pair, one cluster will be randomized to the intervention arm and the other to the comparison arm. Within each selected AWC, 10 children will be randomly sampled from all eligible children in the cluster.

The allocation sequence will be generated by an independent statistician. The allocation code for each of the 60 clusters will be available only to the statistician and shared with the site investigator upon request, ensuring allocation concealment.

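### The cost-effectiveness ratio cannot be computed as written: its denominator counts children by a between-arm difference in means, and the child population for the effect is not stated

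*Protocol article*

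**What the plan says.** The third objective is "To document the incremental cost-effectiveness of the integrated intervention package compared to the existing THR and SBCC strategy in the study districts". Section 2.4.9.5 (Economic evaluation) sets out how this will be done, in three steps.

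- **Cost.** The total for a site is the "sum of the financial and time cost of all activities related to intervention development and implementation". The examples given include the improved THR itself, training, SBCC materials and worker time.
- **Effect.** "Incremental effectiveness will be measured by examining the changes in weight-for-age z-score for children in the intervention and control arms".
- **Ratio.** The incremental cost is divided by the "additional number of children with a mean difference of 0.3 in mean WAZ scores in the intervention arm as compared to the control arm".

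The 0.3 appears in one other place. Section 2.4.6 sizes the trial to "detect a minimum mean difference of 0.3 in mean WAZ score between intervention and comparator arms", with a comparator mean of −1.8 and an SD of 1.0.

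On who receives the costed package, section 2.4.3 states: "All the children aged 6–36 months who live in the selected AWC area, registered with the AWC", whatever their socioeconomic status, "will be eligible to receive the THR and SBCC, according to the allocation arms". On who is measured, there are two groups. For the cohort, section 2.4.7 states "Within each selected AWC, 10 children will be randomly sampled from all eligible children in the cluster". For the survey, section 2.4.3.2 takes every child aged 6–36 months present in the area. WAZ is an outcome in both (section 2.4.5.2).

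**The concern.** A difference in means between arms is one number for a pair of groups. It is not a property of a child, so there is no number of children who have it and no additional number in one arm. The ratio takes the design value from the sample size section and uses it as if it were a child-level threshold. It also breaks with the sentence before it, which treats the effect as a continuous change in WAZ.

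The two halves of the ratio also lack a stated common population. Costs arise for all registered children aged 6–36 months in the cluster, but the section does not say in which children the effect is counted.

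This is the only ratio the article gives for a named objective, and the findings are meant to inform THR reform. With the denominator open, two analysts could report very different costs per unit of benefit from the same data, and the choice could be made after results are seen.

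**Working it through.** **1. Where the 0.3 comes from.** Inputs from sections 2.4.6 and 2.4.11: difference 0.3, SD 1.0, two-sided 5%, power 80%, ICC 0.05, attrition 20%, 10 children per cluster.

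- Individually randomised: n = 2 × (1.960 + 0.842)² × 1.0² / 0.3² = 175 per arm after rounding up.
- With 8 retained per cluster: design effect 1 + 7 × 0.05 = 1.35; 175 × 1.35 = 237 after rounding up; divided by 0.8 this is 296.
- With 10 per cluster: design effect 1.45; 175 × 1.45 = 254 after rounding up; multiplied by 1.2 this is 305, and divided by 0.8 it is 318.

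The stated 300 per arm per site is reproduced closely by 296 or 305. This confirms that the 0.3 is a difference between arm means.

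**2. What the denominator could be.** Take 300 children per arm at one site, a true mean difference of exactly 0.3, and normal distributions.

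| Reading | Calculation | Result |
|---|---|---|
| Literal, arm level | the arm shows the difference or it does not | 300 or none |
| Underweight averted (WAZ below −2) | Φ(−0.2) − Φ(−0.5) = 0.421 − 0.309 = 0.112; × 300 | about 34 children |
| Extra children gaining at least 0.3, low end | SD of change 1.0, control change −0.3: 0.382 − 0.274 = 0.108; × 300 | about 32 children |
| Extra children gaining at least 0.3, high end | SD of change 0.5, control change 0: 0.500 − 0.274 = 0.226; × 300 | about 68 children |

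The second row uses only the figures in section 2.4.6: means −1.8 and −1.5, SD 1.0. The last two rows need an SD of change (0.5 to 1.0) and a mean change in controls (−0.3 to +0.3). The document gives neither, so they are assumptions.

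For the same cost, the ratio differs by up to 300 / 32.4, or about 9-fold, between the literal reading when met and the smallest count.

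**3. What an unscaled cohort count would do.** The document gives about 1,000–1,200 people per cluster and 10 cohort children. The number of children aged 6–36 months is not given, so two assumptions are shown.

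- Age share of 3–6%: 0.03 × 1,000 = 30 to 0.06 × 1,200 = 72 children. Divided by 10, this is 3.0 to 7.2.
- 16–24 births per 1,000 a year over 2.5 years: 1,000 × 0.016 × 2.5 = 40 to 1,200 × 0.024 × 2.5 = 72 children. Divided by 10, this is 4.0 to 7.2.

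If costs for all these children were divided by a count from the 10 alone, cost per unit of effect would be overstated about 3 to 7 times. These are residents. The package goes to registered children, so the true factor may be lower. The distortion affects counts and totals. A mean difference per child paired with a cost per child does not have it.

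**The case against.** The best defence is that the last sentence is loose wording for a child-level count, such as children gaining at least 0.3, and that a full economic analysis plan would define it. It may be meant that way, and an article need not give every detail. But nothing is being faulted for absence here: the article prints a formula, and that formula does not yield a number. The child-gain reading is also only one of several.

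Three stronger readings are tempting and are not supported.

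- **That the third objective cannot be answered.** Table 3 schedules cost data and anthropometry at every assessment, and the sentence before the ratio names a usable effect measure. The printed ratio fails; the objective does not.
- **That the plan sets whole-cluster costs against the effect in 10 children.** Section 2.4.9.5 refers only to children in the two arms. A within-child change and the 0.3 both point to the cohort, but the universal survey measures WAZ too. The text supports only that the population is unspecified, and the several-fold overstatement is conditional on an unscaled cohort count.
- **That the ratio jumps from finite to infinite at 0.3.** If the true effect is 0.3, each site's estimate falls below it about half the time, and 0.5^6 = 1.6% would be the chance that all six sites pass. The text contains no such pass/fail rule, and section 2.4.11 also plans a pooled analysis.

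One caution about the remedy also stands. The cohort is enrolled at 6–18 months, and the survey includes children regardless of registration, so neither matches the costed population exactly.

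**Conclusion.** The concern holds for the ratio as written. Its denominator treats an arm-level design difference as something a child has, and it disagrees with the effect measure in the sentence before it. That conclusion needs no assumption beyond the text.

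The size of the ambiguity is large: 300 or none, about 34, or about 32 to 68 children per 300 per arm. The last range rests on assumed values for the SD of change and the change in controls, and the calculated counts assume normal distributions and a true effect of 0.3. The 3- to 7-fold overstatement is a conditional risk. It rests on age shares or birth rates that are not in the document and on a cohort count being used without scaling.

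The primary outcome, sample size and randomisation are unaffected.

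**What to change.** Replace the last sentence of section 2.4.9.5 with a defined ratio: incremental cost per child served, divided by the between-arm difference in mean WAZ change from baseline to 18 months, reported with a confidence interval. Drop the 0.3 from the ratio.

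State the child population used for costs and for effects. If the cohort effect, from children enrolled at 6–18 months, is applied to all beneficiaries aged 6–36 months, state that as an assumption. Underweight cases averted among all children aged 6–36 months may be added as a secondary ratio, noting that the survey includes unregistered children.

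The cost is one reworded paragraph and an explicit extrapolation assumption. The cost, WAZ and survey data are already planned, so nothing new has to be collected. The change should be made before results by arm are seen.
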